#### Training of study interventionists

The interventionists for the project are advanced doctoral students with experience delivering CBT-based health interventions and/or trauma-focused therapies (depending on the protocols they are trained to conduct). The health behavior interventionists are familiar with the healthy lifestyle intervention literature and develop a thorough understanding of the protocol for PTSD patients by reviewing the manual and meeting with the PI for training. Interventionists are encouraged to meet with the PI throughout intervention delivery to affirm their knowledge and confidence with the protocol and address any questions that might relate to participant-specific presentations.

For interventionists who conduct the standard trauma therapies, the PI reviews evidence-based conceptual and intervention models of trauma-focused treatment for PTSD, including Cognitive Processing Therapy (Resick et al., 2002; Resick and Schnicke, 1992), Prolonged Exposure Therapy (Foa et al., 2007; McLean and Foa, 2024), and as applicable for participants with a presentation consistent with the literature on complex-PTSD, Contextual Trauma Therapy (Gold and Quiñones, 2020). Trauma therapists are encouraged to review treatment-specific readings for the various models of treatment reviewed during training and meet with the PI and project coordinators (designated as lead interventionists) to discuss treatment options for assigned participants. Trauma therapists select treatment approaches based on the clinical presentations of participants and collaboration with participants about the various options for care. Given the literature suggesting increased rates of drop-out in exposure-based treatment, it was imperative that trauma therapists have a strong rationale for this approach, a deep understanding of its implementation, and the ability to educate the participant about the treatment delivery (Imel et al., 2013). Trauma therapists are invited to discuss their approaches to treatment, ask questions about intervention implementation and participant clinical presentations, as well as discuss relevant research on PTSD treatment during monthly research lab meetings, in one-on-one meetings with the PI, and in peer supervision meetings with the research coordinators.

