#### Health behavior/lifestyle intervention

The healthy lifestyle intervention is a 12-session program with sequential but overlapping modules for increasing physical activity, enhancing good nutrition, improving sleep, and improving stress management. The sessions are conducted individually and are held weekly for 90 min. Participants have the option of conducting the intervention sessions (health behavior and/or trauma therapy sessions) in-person or virtually via a secure HIPAA-compliant Zoom platform. The length of the program was determined by the need to be long enough to effectively address the 4 modules, while also being relatively brief to minimize burden for participants and enhance likelihood of compliance. For the current project, the decision to utilize 12 sessions was also informed by positive feedback from the participants and interventionists in the pilot study regarding the program length.

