#### Summary

Completing 162 protocols (81 per condition) with minimum power of 80% and alpha level of 0.05 will permit detection of a moderate effect of 0.47 or greater (Cohen, 1988). Therefore, this sample size would permit detection of the smallest effect estimated above for lipids (*d* = 0.50) and will be conservative for the projected large effects for some of the estimates above. Participants in the health behavior intervention condition (experimental group) are considered treatment completers if ≥75% of sessions are attended.

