#### Data analysis plan

Preliminary analyses will be conducted to examine distributions, detect outliers, and compare the study groups on demographic variables, comorbid psychopathology, type of trauma therapy received, smoking, and alcohol use. Based on the randomization, no differences for demographic (e.g., age, gender) or other baseline comparison variables are expected. In addition, gender is not predicted to interact with the main study effect (condition). If there are group differences in any of the baseline comparison/control variables, the respective variable(s) will be treated as a control in the analyses.

A between-groups approach is used, with study condition as the independent variable (IV) and changes in the outcomes as the dependent variable(s) (DVs). The outcomes will be analyzed using linear mixed-effects regression. This approach is recommended for between-group longitudinal trials with follow-up time points to model changes over time, to incorporate all available data at each time point, and to account for non-independence of observations inherent in repeated-measures data (Verbeke and Molenberghs, 2000). A piecewise model will be specified to model change during distinct time periods of the trial (Raudenbush and Bryk, 2002). Separate slopes will be provided for the pre- to post-treatment phase, and each follow-up point (pre- to 6-month follow-up, and pre- to 12-month follow-up). Multivariate analyses will be used for each hypothesis to control for type 1 error by testing the DVs together. Significant multivariate effects will be followed with univariate tests.

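### The health programme is delivered by student interventionists in one arm only, but the model and power statement allow for no clustering by interventionist, so the nominal 5% level and 80% power at d = 0.47 are not assured

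*Protocol article*

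**What the plan says.** Protocol article, Training of study interventionists: "The interventionists for the project are advanced doctoral students with experience delivering CBT-based health interventions" (the same sentence adds that some deliver trauma therapy instead or as well). Health behavior/lifestyle intervention, on the twelve-session programme: "The sessions are conducted individually and are held weekly for 90 min". Study design: during the comparison, controls receive assessments and usual-care psychotherapy but no health programme. They may take it up only after their control participation has ended.

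Data analysis plan: outcomes are analysed by linear mixed-effects regression with piecewise change over time. One reason given for the method is "to account for non-independence of observations inherent in repeated-measures data". No interventionist or therapist effect is mentioned.

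Summary of the power section: for 162 completers, split equally between the arms, and "minimum power of 80% and alpha level of 0.05", the article states that the sample size "will permit detection of a moderate effect of 0.47 or greater". It concludes that "this sample size would permit detection of the smallest effect estimated above for lipids", d = 0.50. No ICC, caseload or design effect appears.

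**The concern.** The programme depends on the person delivering it. Interventionists walk with participants, help set goals and work through nutrition, sleep and stress problems with them. Some interventionists may get better results than others, and participants who share one would then have correlated outcomes. This source exists in the experimental arm only, so the design is partially nested.

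A participant-level random effect does not capture variation that is shared across participants. If that variation is present and left out of the model, the arm contrast is given too small a standard error. Confidence intervals are then too narrow and the type I error exceeds 0.05. A sample size worked out for independent participants also gives less power than it appears to.

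**Working it through.** **Inputs from the article (power Summary).** 81 completers per arm, alpha 0.05, power at least 80%, d = 0.47, smallest projected effect d = 0.50. Sidedness is not stated; two-sided is assumed.

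**Assumed, because the article gives neither.** Number of interventionists k (4 to 20) and ICC ρ (0.02 to 0.10), with equal caseloads m = 81/k.

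**Step 1: the plan's own figure.** Under independence SE = √(2/81) = 0.157.
- Power at d = 0.47: Φ(0.47/0.157 − 1.96) = 84.9% (84.4% by the t-test).
- Effect detectable with 80% power: (1.96 + 0.84) × 0.157 = 0.44.

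So 80% as a minimum is true under independence, with about 5 points to spare.

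**Step 2: clustering in the experimental arm only.**
- Design effect in that arm: DE = 1 + (m − 1)ρ.
- SE of the arm difference: √((1 + DE)/81).
- Ratio to the independence SE: √((1 + DE)/2).
- True alpha of the unadjusted test: 2[1 − Φ(1.96/ratio)].
- Power: by normal approximation, and by noncentral t with Satterthwaite degrees of freedom (k − 1 in the clustered arm).

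Example, k = 8 and ρ = 0.05: m = 10.1; DE = 1 + 9.125 × 0.05 = 1.46; SE = √(2.456/81) = 0.174; ratio 1.108. Alpha = 2[1 − Φ(1.77)] = 7.7%. Power = Φ(0.47/0.174 − 1.96) = 77.0%. Detectable d = 2.80 × 0.174 = 0.49.

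| k | m | ICC | DE | SE ratio | True alpha | Power at 0.47, normal | Power at 0.47, t |
|---|---|---|---|---|---|---|---|
| 4 | 20.2 | 0.02 | 1.39 | 1.092 | 7.3% | 78.2% | 68.1% |
| 8 | 10.1 | 0.02 | 1.18 | 1.045 | 6.1% | 81.7% | 78.2% |
| 8 | 10.1 | 0.05 | 1.46 | 1.108 | 7.7% | 77.0% | 72.6% |
| 8 | 10.1 | 0.10 | 1.91 | 1.207 | 10.4% | 69.8% | 64.3% |
| 10 | 8.1 | 0.02 | 1.14 | 1.035 | 5.8% | 82.4% | 79.8% |
| 10 | 8.1 | 0.05 | 1.35 | 1.085 | 7.1% | 78.7% | 75.5% |
| 20 | 4.0 | 0.05 | 1.15 | 1.037 | 5.9% | 82.2% | 80.9% |

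The t column also contains the cost of few clusters. With k = 8 and ICC 0 it is already 82.1%.

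**Step 3: where the spare power runs out.** By the normal approximation, 80% power at d = 0.47 requires (1 + DE)/81 ≤ (0.47/2.80)², that is DE ≤ 1.28. This is exceeded once the ICC is above about 0.015 (k = 4), 0.031 (k = 8), 0.039 (k = 10) or 0.092 (k = 20).

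**Step 4: the d = 0.50 claim.** Independence gives 88.9%. With ICC 0.05, k = 8 gives 81.9% (normal) or 77.8% (t), and k = 10 gives 83.5% or 80.5%. With k = 8 and ICC 0.10 the figures are 75.1% and 69.7%.

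**The case against.** **The sentence on repeated measures is a reason for choosing mixed models, not a list of random effects.** An interventionist effect would fit within the named method, and a fuller plan that is not shown may include one. This stands in part: nobody can say from the article that the effect has been ruled out. But the article gives a rationale with one source of dependence and a power figure with no design effect, and both can be judged as written.

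**The pool may not be small.** The article gives no number of interventionists, no caseload and no ICC, and does not say in terms that a participant keeps one interventionist throughout. This stands. With 20 interventionists and ICC 0.05 the error is minor.

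**A reader might infer that the stated power is too high.** The documents do not support that. The article claims a minimum of 80%, independence gives about 84%, and the difference absorbs mild clustering. Under the plausible assumptions above, power falls on either side of 80%. Nor is the conclusion about d = 0.50 overturned: with about 10 participants per interventionist and ICC 0.05, the detectable effect is about 0.49 by normal approximation, although the t-based power at 0.50 with k = 8 is slightly below 80%.

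**Controls are not simply unclustered.** The Participants section says that the project supplies trauma therapy to those without it, and students deliver it. Such therapists may treat people in both arms. This stands, and it means that controls should not be described as clusters of one without qualification. A therapist who treats both arms does not inflate the arm contrast in the way one-arm nesting does, and this second source does not remove the first.

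**Conclusion.** The point holds in conditional form. The tested programme is delivered by interventionists in one arm only, and neither the model description nor the power calculation allows for this. For any positive interventionist ICC, the analysis as described understates the standard error of the arm contrast. How much is unknown, because k and the ICC have to be assumed: true alpha is about 6 to 8% for 8 to 10 interventionists with ICC 0.02 to 0.05, and power at d = 0.47 is about 73 to 82%, against about 84% under independence. Fewer interventionists or a higher ICC make it worse; 20 interventionists make it small. The figures also assume equal caseloads, one interventionist per participant and a simple two-group contrast. This is a worthwhile, inexpensive improvement and not proof that the trial is underpowered.

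**What to change.** 1. Record the health interventionist ID for each experimental participant, and the project trauma therapist ID where there is one. The trial is described as ongoing, so this can still be done.
2. Add to the Data analysis plan: *The mixed model will include a random effect for health interventionist in the experimental arm (partially nested model), with small-sample degrees of freedom. A sensitivity analysis will also include the project trauma therapist, who may treat participants in both arms.*
3. Restate the detectable effect in the power Summary over a range of assumed caseloads and ICCs, for example about 0.49 by normal approximation at 10 participants per interventionist and ICC 0.05, in place of a single figure under independence. Report the actual number of interventionists and their caseloads.

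The cost is the provider ID variables, a short addition to the plan, slightly wider intervals and a slightly less favourable stated detectable effect. No extra participants are needed. If the ICC proves close to zero, little is lost beyond some degrees of freedom.

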Stress-related and emotional factors have been identified as an early candidate mechanism for PTSD/CVD relationships, with various responses to acute and chronic stress being implicated in this relationship (Smith et al., 2020a,b). For example, PTSD severity was shown to be related to delayed cardiovascular recovery following a general (not trauma-related) laboratory oral speaking stressor (Kibler, 2018). Delayed cardiovascular recovery in the lab has been associated with greater carotid intima-media thickness, as well as elevated resting blood pressure measured 3 years after lab assessment of recovery (Steptoe et al., 2006; Steptoe and Marmot, 2005). Perceived threat (a pervasive maladaptive cognitive response in PTSD) mediated these physiological disruptions (Kibler, 2018). Research has identified cognitive appraisals, including perceived threat, as key factors to address in PTSD (Iverson et al., 2015). Although the implications of cognitive appraisals for health behaviors in PTSD have not been adequately researched, relationships of appraisals to stress are evident, and Lazarus and colleagues' Cognitive Appraisal Theory (Lazarus and Folkman, 1984) suggests that the types of disrupted cognitions evident in PTSD may interfere with the pursuit of healthy behaviors such as physical activity (Folkman et al., 1986). Interventions to address cognitive appraisals may reduce stress-related CVD risk in PTSD by enhancing the ability to cognitively cope with stressors and engage in healthy behaviors.

The purpose of the present paper is to detail our approach to the study protocol, focusing on the scientific rationale and methodological details. It is hypothesized that the healthy lifestyle intervention will result in greater improvement in vascular function (i.e., endothelial function, arterial stiffness), physical activity, nutrition, sleep, and stress, above and beyond the effects of standard trauma therapy.

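### The multivariate test followed by unadjusted univariate tests does not control type 1 error within a hypothesis once the set has three or more outcomes, or once three time contrasts are tested

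*Protocol article*

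**What the plan says.** The Data analysis plan gives both a procedure and its purpose: "Multivariate analyses will be used for each hypothesis to control for type 1 error by testing the DVs together". The next step reads "Significant multivariate effects will be followed with univariate tests", and no adjusted level is attached to it.

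The Introduction hypothesises that the intervention "will result in greater improvement in vascular function (i.e., endothelial function, arterial stiffness), physical activity, nutrition, sleep, and stress". That is one sentence naming five domains, which are not numbered as separate hypotheses. Vascular function is defined there by two measures. The section on outcome assessment sessions lists four aspects of sleep: quantity, efficiency, quality and restfulness.

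On time, the plan says "Separate slopes will be provided for the pre- to post-treatment phase, and each follow-up point (pre- to 6-month follow-up, and pre- to 12-month follow-up", which makes three contrasts from baseline. The only significance level in the article is in the power Summary: "minimum power of 80% and alpha level of 0.05 will permit detection of a moderate effect of 0.47 or greater", with 81 completers per condition. Sidedness is not stated.

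**The concern.** The multivariate test acts as a gate. If nothing in the set is affected, the gate opens in only 5% of trials and false univariate claims stay below that. If one outcome truly responds, the gate opens because of that outcome, and the unaffected outcomes pass through and are each tested at the full 0.05. That is weak control: it holds under the complete null and fails under partial nulls.

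The partial null is a realistic case here. The article projects effects of d = 0.67 to 1.41 for sleep quantity and quality, and the Discussion says the pilot had its greatest impact on sleep and physical activity. The gate therefore protects least where effects are expected. A paper could report a benefit on sleep efficiency or restfulness, say, as having passed a type 1 error safeguard when in effect it had an ordinary unadjusted test.

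**Working it through.** **Inputs.** From the article: 81 per arm; level 0.05 (taken as two-sided); four sleep outcomes; d = 0.67 and 1.41; three contrasts; five domains. Assumed: equal correlations of 0, 0.3 and 0.5 between outcomes; the four sleep aspects form one set; univariate tests run at 0.05.

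**The plan's own figure.** Per-arm size for d = 0.47 at 80% power: 2 × (1.960 + 0.842)² / 0.47² = 71.1, so 72. At 81 per arm, 0.47 × √(81/2) = 0.47 × 6.364 = 2.991, and 2.991 − 1.960 = 1.031, which gives 84.9% power. The statement is true as a minimum of 80%. It uses the full 0.05 for one comparison.

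**Why two outcomes are safe and three are not.** With two outcomes at one contrast, the joint null is tested by the multivariate test and each single null by its own t test. Every intersection is covered, so this is a closed test and holds 0.05. With three or more, the intersections of intermediate size (pairs, for example) are never tested, and control is lost.

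**Simulation.** Hotelling test at 0.05, then t tests at 0.05; 20,000 simulated trials per setting; one outcome moved by d = 0.67. Ranges are over the three correlations.

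| Outcomes in set | Multivariate test significant | At least one false univariate claim |
|---|---|---|
| 2 | 0.972-0.995 | 0.049-0.051 |
| 3 | 0.957-0.996 | 0.088-0.096 |
| 4 | 0.939-0.996 | 0.122-0.142 |

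With d = 1.41 the gate always opens, and four outcomes give 0.127-0.144. Repeat runs reached 0.15, hence 12-15%. With no effect on any outcome, the rate is about 0.04-0.05 for every set size.

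**Check by formula.** With the gate open and three independent null outcomes: 1 − 0.95³ = 0.143. In the favourable direction only: 1 − 0.975³ = 0.073, hence about 6-8%. If sleep quantity and quality both respond, two nulls remain: 1 − 0.95² = 0.098, still about twice the nominal level.

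**Three contrasts.** If each contrast has its own multivariate test at 0.05 and nothing is affected, the chance of at least one significant result within one hypothesis is 1 − 0.95³ = 0.143 if independent, and about 0.11-0.13 with correlations of 0.5-0.7 over time. If one multivariate test covers all three contrasts, vascular function becomes a set of 2 × 3 = 6 and the argument for three or more applies. The article does not say which is meant; control fails either way.

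**Five domains.** With all five null, one contrast and 0.05 each: 1 − 0.95⁵ = 0.226 if independent, and about 0.18-0.21 with correlations of 0.3-0.5.

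**With Holm instead.** In the three- and four-outcome settings above, the rate returns to 0.04-0.05.

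**The case against.** The best defence has four parts.

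- **Vascular function is safe at a single contrast.** This stands. A reader might infer that the rule fails in every hypothesis. It does not: two outcomes at one contrast hold 0.05, and stress has a single named instrument, so it has no multiplicity at one contrast if one score is used. The protection goes once three contrasts are tested.
- **Control across domains is never promised.** This stands. The sentence speaks of each hypothesis, and the count of five is read from a list. If all domains were one hypothesis, the inflation across hypotheses would vanish and the inflation within the set would grow.
- **A false claimed benefit is not shown to be likely.** This stands. A reader might infer it by combining five domains with three contrasts, but such a total assumes that every null is true and that each contrast has its own test. The tests are also taken as two-sided, so false benefits are only about half of the false claims.
- **A multivariate analysis need not discard incomplete participants.** This stands. A reader might see a conflict with the stated use of all available data, but the article names no classical multivariate test, and a multivariate mixed model would fit both statements.

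It can also be said that a condensed article leaves details to the full plan. That is fair for the make-up of each outcome set and for the choice of primary outcome. It does not rescue a rule that the article states together with the property it is meant to have: an analysis plan that carried the rule over unchanged would carry the fault.

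**Conclusion.** The concern holds in limited form. As written, the rule controls type 1 error within a hypothesis only if no outcome is affected, or if there are at most two outcomes at one contrast. For four sleep outcomes with one responding, the error rate is about 12-15% against a nominal 5%, and about 6-8% for a false benefit. Testing three contrasts without a link removes control for the vascular hypothesis as well. The missing link across the five domains is a gap (about 18-23% for at least one significant multivariate test at one time point if all are null), not a false statement.

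These sizes rest on 81 per arm, two-sided tests at 0.05, assumed correlations, and the four sleep aspects forming one set. The direction of the conclusion does not depend on the exact correlations.

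**What to change.** Within each hypothesis, replace the unadjusted univariate tests with Holm-adjusted tests from the mixed model, taken over the outcomes and time contrasts that carry a claim. Alternatively, name one contrast as confirmatory and report the others as estimates with intervals.

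Then settle the scope in one of two ways before data are examined. Either restate the sentence so that it claims control per hypothesis only, or have the sponsor name a primary hypothesis and visit and test the other hypotheses only after it, within one overall 0.05. Which hypothesis is primary is the sponsor's scientific choice; the article does not make it.

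The cost is wording in the analysis plan, some power for single outcomes, and fewer outcomes that can carry a confirmatory claim. For four outcomes at one contrast, Holm's strictest step is 0.05/4 = 0.0125 (z = 2.498). At 81 per arm and d = 0.50, 0.50 × 6.364 = 3.182. Power is then Φ(3.182 − 2.498) = 75%, against Φ(3.182 − 1.960) = 89% for a test at 0.05 with no gate. At d = 0.67 the figures are 96% and 99%. The present rule already gives up some of that power, because the multivariate test must be significant first. Holm over all three contrasts costs more, which is a reason to name one.
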